## Methods

### The NORMA study

The NORMA study consists of WP1; a clinical observational trial (**Fig 1**), WP2; in vitro experiments (**Fig 2**), and WP3; animal experiments (**Fig 3**). An overview of all WPs is presented in **Fig 4**. The NORMA study is led by the Norwegian University of Life Sciences (NMBU) and conducted in collaboration with seven specialized inpatient EDs treatment units across six hospitals in Norway, located in Oslo, Bergen, Vikersund, Levanger, Bodø, and Gjøvik. Additional collaborators are The University of Oslo, Karolinska Institute and the Norwegian user organizations for eating disorders ROS and SPISFO, which has been involved in the planning of the study. WP1 includes a cross-sectional design that will investigate the microbial composition of the gut in patients with AN in comparison with HCs, and a clinical observational trial that will investigate how the composition is affected by standard care treatment in AN longitudinally (one group time-series design). We will then apply preclinical models in WP2 (in vitro fermentation experiments) and WP3 (animal experiments) based on fecal material from WP1. The first results are expected to be generated during second quarter of 2026.

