Blood serum is chosen for biobanking due to its accessibility and suitability for analyzing a wide range of biomarkers, including inflammation- and appetite-related markers. To ensure proper handling and storage of blood samples, all specimens collected at local hospitals will be processed at accredited laboratories and stored according to standard operating procedures (SOPs). Key biomarkers that will be analyzed in serum samples at the local laboratories (for patients with AN) or at the Department of Medical Biochemistry at Oslo University Hospital (for HCs) are presented in **Table 2**. Additional analyses will include, but not be limited to, biomarkers related to appetite and satiety (e.g., ghrelin, adiponectin, GLP-1, and leptin), inflammation (e.g., calprotectin, IL-1β, MCP-1, and RANTES), and gut permeability (e.g., LBP and I-FABP).

**Table 2 pone.0342275.t002:** Key biomarkers to be analyzed in blood serum samples from patients with anorexia nervosa and healthy controls the clinical observational trial in work package 1 of the NORMA study.

Biomarker group	Biomarkers	Rationale
Hematology	Hemoglobin (Hb), mean corpuscular volume (MCV), mean corpuscular hemoglobin (MCH), hematocrit (HCT), erythrocyte volume fraction (EVF), thrombocytes, B-differential count, ferritin, international normalized ratio (INR)	Nutrient status (anemia), dehydration, infections/inflammatory state
Hormones	thyroid-stimulating hormone (TSH), triiodothyronine (T3), thyroxine (T4), parathyroid hormone (PTH)	Metabolism, hypo-and hyperthyroidism
Electrolytes	Sodium, calcium, potassium, magnesium, phosphate, chloride, Osmolality/osmol gap	Nutrients status, dehydration, electrolyte imbalance, Risk of refeeding syndrome
Lipids	Total cholesterol, low-density lipoprotein (LDL), high-density lipoprotein (HDL), triglycerides	Cholesterol status, cardiovascular risk
Metabolites	Creatinine, bilirubin, carbamide	Kidney function, muscle metabolism, liver disease
Enzymes	Alanine transaminase (ALT), aspartate transaminase (AST), gamma-glutamyl transferase (GGT)*, lactate dehydrogenase (LDH), creatine kinase (CK), amylase, alkaline phosphatase (ALP)*, glomerular filtration rate (GFR)*	Liver and kidney function, muscle injury
Proteins	Albumin, C-reactive protein (CRP)	Nutrient status and inflammatory state
Vitamins	Vitamin D*, cobalamin (B12), folate	Vitamin status, bone health, anemia

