#### Hypotheses and planned statistical data analyses in WP1.

The clinical observational trial in WP1 is designed to test the following hypotheses.

WP1, Hypothesis 1: The gut microbiota in patients with AN is different from that of HCs. We will compare different indices of alpha diversity, investigating both microbial richness and evenness, and different measures of beta diversity. Also, differences in bacterial abundances at various taxonomic levels (e.g., phylum, class, order, family, and genus) will be investigated using conventional statistical approaches as well as more advanced multivariate methods.WP1, Hypothesis 2: Inpatient treatment of patients with AN combining cognitive treatment with re-nutrition strategies will change the gut microbiota in a more normalized direction (more similar to HCs). Mixed models will be applied to statistically analyze the effect of time on different indices of alpha diversity and bacterial abundances at various taxonomic levels (e.g., phylum, class, order, family, and genus) with and without adjusting for baseline characteristics such as age and BMI. Differences in the overall bacterial communities between the patients with AN at the different visits and HCs based on the beta diversity measures will be assessed using methods such as global permutation based multivariate analysis of variance (PERMANOVA).WP1, Hypothesis 3: Gut microbiota composition in patients with AN at TP1 (before treatment) is associated with serum biomarkers such as biomarkers of appetite regulation and inflammation, dietary characteristics, GI issues, and mental issues, and can be used to predict treatment success in terms of improved BMI and EDE-Q-scores. Associations between relevant parameters will be analyzed using multivariate analysis such as principal components analysis (PCA), canonical variate analysis, independent components analysis, and multivariate regression. Regression models will be used to investigate associations between microbial diversity and clinical outcomes, adjusting for age and BMI. Machine learning approaches such as partial least squares regression, gradient boosting, or artificial neural network algorithms will be used to predict the response variables (clinical outcomes and treatment success), from the large set of predictor variables; microbial taxa, gene, or pathway content.WP1, Hypothesis 4: Changes in microbiota composition during inpatient treatment towards that of HCs are associated with improvements in BMI as well as improvements in dysregulated serum biomarkers, GI complaints, and mental health. Associations will be analyzed using similar strategies as described in hypothesis 3.

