Due to the limitations of the previous studies on gut microbiota in patients with AN, there is a clear need for larger-scale, longitudinal studies. While existing research suggests that microbial mechanisms may play a role in the etiology of AN [18,26], more evidence is needed to determine whether gut microbiota dysbiosis is a consequence of the disorder, a contributing factor to its onset, or involved in its maintenance. The NORMA study will address these gaps by combining a well-powered clinical observational trial accompanied by animal and in vitro experiments, integrating detailed dietary and medical data, and standardized and validated methodologies. This approach allows for a more accurate assessment of microbiota changes over time but also provides insights into the underlying mechanisms. The remainder of the discussion outlines the core strengths of the NORMA study, as well as key methodological aspects to consider in relation to the current research protocol.

In addition to being one of the largest longitudinal studies of gut microbiota in AN—including patients from six hospitals across Norway— the NORMA clinical trial benefits from several major methodological strength: firstly, the high adherence of all patients—primarily inpatients—to specialized treatment programs for EDs throughout the research period. This adherence results in a consistent treatment framework, including structured routines, and dietary interventions across the patient cohort. Although minor differences in therapeutic approaches and nutritional treatment will exist across hospitals, the overall consistency will reduce the risk of confounding factors. This uniformity represents a significant methodological advantage compared to studies primarily involving outpatient populations, where treatment heterogeneity is typically greater.

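### The H3 and H4 regressions name age and BMI as covariates but not treatment unit, so unit differences could pass for microbiota associations, mainly in H4; adding unit is a cheap improvement.

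*Protocol article*

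**What the plan says.** All references are to the protocol article.

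- **H3 regressions** (Hypotheses and planned statistical data analyses in WP1): "Regression models will be used to investigate associations between microbial diversity and clinical outcomes, adjusting for age and BMI". H3 also holds that baseline microbiota "can be used to predict treatment success in terms of improved BMI and EDE-Q-scores". No adjustment is stated for its multivariate and machine-learning analyses.
- **H4** (same section): "Associations will be analyzed using similar strategies as described in hypothesis 3". H4 relates change in microbiota to improvement in BMI, serum biomarkers, GI complaints and mental health.
- **H2, for contrast** (same section): its mixed models are run "with and without adjusting for baseline characteristics such as age and BMI", which is worded as an open list.
- **Units** (The NORMA study): "seven specialized inpatient EDs treatment units across six hospitals in Norway, located in Oslo, Bergen, Vikersund, Levanger, Bodø, and Gjøvik". Study participants adds that inpatient, day-treatment and sequential-admission patients are all eligible.
- **Differences between hospitals** (Discussion): "minor differences in therapeutic approaches and nutritional treatment will exist across hospitals". The same sentence argues that overall consistency lowers the risk of confounding.
- **Timing of baseline** (Overview of study design and procedures): TP1 falls before treatment starts and/or within the first week of admission.
- **Laboratories** (Fasting blood samples): the Table 2 markers of patients are measured at local laboratories, while serum aliquots from all hospitals are biobanked centrally.

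**The concern.** H3 and H4 compare patients with one another. If units differ both in the microbiota measure and in the outcome, patients from the same unit share both differences, and a regression without unit reads them as an association. Age and BMI do not remove this.

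The route is clearest in H4. A unit whose re-nutrition is faster or differently composed can change the microbiota more and also raise BMI or ease GI symptoms more. The Background itself names diet as the strongest modulator of the gut microbiota. Such a pattern would look like support for H4 even if the microbiota played no part.

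In H3 the predictor is measured at TP1, so a unit's treatment acts mainly on the outcome. What can reach the predictor is region, case-mix between units, and diet during the first days after admission. The H3 prediction models have a related weakness: they can learn features that identify the unit and present the unit's outcome level as prediction from the microbiota.

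At stake is how the WP1 association findings are read, not the primary AN–HC comparison.

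**Working it through.** **The plan's own figures.** The sample size section gives 79 per group for the AN–HC comparison and about 10% drop-out. 79 / 0.90 = 87.8, so 88; the plan takes 90, and 90 × 0.90 = 81 evaluable, which covers 79. There is no calculation for H3 or H4. Both n = 90 and n = 81 are used below.

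**Inputs from the document.** Seven units; age and BMI as covariates; alpha 0.05 (taken as two-sided).

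**Assumed inputs, since the document gives none.**
- Unit sizes at n = 81: equal (12, 12, 12, 12, 11, 11, 11) or unequal (28, 18, 12, 8, 7, 5, 3).
- Unit sizes at n = 90: unequal (30, 18, 12, 10, 8, 7, 5).
- The share s of variance that unit explains in the predictor x and in the outcome y.

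**False-positive simulation.** x = √s·(unit effect) + √(1−s)·(individual part), and y likewise, with independent unit effects and no true association. Ordinary least squares of y on x, age and BMI is compared with the same model plus six unit indicators. There were 6,000 runs per setting at n = 81 (Monte Carlo standard error √(0.05 × 0.95 / 6,000) = 0.3 points). The n = 90 column gives the range over repeated runs.

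| Unit share in x and y | n = 81 equal | n = 81 unequal | n = 90 unequal | n = 81 with unit term (equal / unequal) |
|---|---|---|---|---|
| 0% | 5.3% | 4.8% | – | 5.2% / 4.6% |
| 2% | 4.8% | 5.2% | – | 4.9% / 5.3% |
| 5% | 5.1% | 5.4% | 5.0–5.8% | 4.8% / 5.5% |
| 10% | 6.1% | 6.3% | 6.0–6.2% | 4.9% / 5.3% |
| 20% | 8.7% | 10.4% | 10.2–10.4% | 5.5% / 5.0% |
| 30% | 14.8% | 16.0% | 15.9–16.2% | 4.7% / 5.5% |

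**Unequal shares, closer to H3** (n = 90, 8,000 runs; share in microbiota / share in outcome): 0% / 20% gives 5.3%; 2% / 20% gives 5.4%; 5% / 20% gives 6.5%; 10% / 30% gives 9.0%. Both shares must be appreciable before the error rate moves.

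**Limits of the simulation.** Unit effects in x and y are drawn independently. If one feature of a unit, such as its re-nutrition regime, drives both in H4, they would be correlated and the inflation larger; this was not simulated. The restored error rate applies to unit indicators; a random intercept was not simulated.

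**Cost in power.** For an assumed partial correlation r = 0.30, df = n − k − 2, with k = 2 (age, BMI) or k = 8 (plus six indicators), and noncentrality = r/√(1−r²) × √df = 0.3145 × √df.

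- n = 90: df 86, noncentrality 2.92, power 82.2%; with unit df 80, noncentrality 2.81, power 79.4%. Loss 2.8 points.
- n = 81: df 77, noncentrality 2.76, power 77.8%; with unit df 71, noncentrality 2.65, power 74.3%. Loss 3.5 points.

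**The case against.** **This is a condensed article.** Naming two covariates does not exclude others, and H4 promises similar strategies rather than the same model. That is fair, and the full analysis plan may include unit. But the H3 sentence names its covariates without the open wording used for H2 in the same section, and the Discussion answers differences between hospitals by appeal to consistency, not by adjustment. The stated set can be improved as it stands.

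**The authors call the differences minor.** If that holds for microbiota and outcomes alike, the inflation is negligible, as the 2–5% rows show. No data are offered either way. This objection limits the size of the concern without removing it.

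**Adjusting can remove real signal.** If a unit's regime changes the microbiota and that change improves the outcome, a unit term discards this part of the H4 association. This stands, and it is the reason to show both models.

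A reader might also infer stronger claims that the documents do not support:

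- *Unit treatment confounds H3 as fully as H4.* Baseline microbiota is sampled before treatment or within the first week, which leaves little time for unit nutrition to shape it.
- *Laboratory differences distort these regressions generally.* BMI, EDE-Q and GI scores are not laboratory results. The appetite markers and most of the inflammation markers are listed apart from the local panel. A constant laboratory offset cancels in within-patient change if the same laboratory measures every time point. The laboratory route is therefore limited to cross-sectional H3 associations with locally assayed Table 2 markers.
- *Patient–control biomarker contrasts are compromised.* No such contrast is among H1 to H4, and the article does not define a dysregulated marker by one.
- *H2 has the same defect.* Its time effect is within patients, and its covariate list is open.

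**Conclusion.** The concern holds in a limited form. The article states age and BMI as the covariates for the H3 regressions, carries the approach to H4 and names treatment unit nowhere in the WP1 analyses, although it recruits from seven units that it says differ somewhat in therapy and nutrition. H4 is the analysis most exposed; H3 is exposed only through region, case-mix and first-week diet.

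The size is unknown. Error rates of 10–16% need unit to explain 20–30% of the variance in both variables, which would sit poorly with differences described as minor. At 5–10% the rate is about 5–6%. These figures rest on assumed unit sizes, assumed and mostly equal shares, and independent unit effects. They show what could happen, not what will.

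This is a cheap improvement to association analyses, not an error that undermines the trial.

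**What to change.** - Add treatment unit to the H4 and H3 regressions, as a fixed effect or random intercept, pooling very small units. At the least, state this as a sensitivity analysis reported beside the age and BMI model.
- In H4, show both results and say that the model with unit indicators reflects within-unit association only.
- Check the H3 prediction models with validation folds grouped by unit, so that no unit appears in both training and test data.
- For cross-sectional H3 associations with locally assayed Table 2 markers, the same unit term also absorbs laboratory differences; no separate step is needed.

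Cost: a change of wording, since recruitment runs through the units and unit is therefore known. It uses up to six degrees of freedom, takes about 2–4 points of power at a correlation of 0.3, and gives up between-unit variation in H4, which may include some genuine signal.

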
### The in vitro experiments (WP2)

#### Experimental groups.

To test the ability of the fecal microbes to ferment prebiotics, processed anaerobic fecal samples from patients with AN and HCs, collected in WP1 (see section “Fecal samples”) will be cultured in vitro as part of WP2. We will use acetylated galactoglucomannan as the pioneer prebiotic supplement and test impact on the microbial communities using fecal samples from four patients with AN and four HCs (**Fig 2**).

#### Bioreactors.

The bioreactors to be used in the WP2 experiments are produced in-house and consist of a double-jacketed stainless-steel vessel with a lid made of polyether ether ketone (PEEK), containing connection ports for gas, acid and base, and a gas-sealed septum sampling. The bioreactors will be pH-controlled (6.8 ± 0.2 by automatic addition of 1 M HCl and 1 M NaOH), the headspace will be continuously flushed with N_2_ gas (O_2_ < 5 ppm), the temperature will be maintained at 37°C via a circulation bath (Thermo Fisher Scientific Inc.), and the content will be stirred at 300 rpm.

#### Preparations.

Sterile basal fermentation media containing prebiotics (0.5% w/v) or ddH_2_O as control will be made according to Table 3, adjusted to pH 6.8, and 70 mL will be transferred to each of the autoclaved bioreactors in a sterile laminar flow hood. The bioreactors with media, alongside HCl and NaOH, will then be placed in an anaerobic chamber (Whitley A85 Workstation; 85% N_2_, 5% CO_2_, 10% H_2_, 37°C) for at least 12 hours to become anaerobic. Sterile pH probes will be inserted into the bioreactors before inoculation. The processed anaerobic fecal samples from WP1 will be thawed in the anaerobic chamber, and optical density (OD_600_) will be measured and used to adjust inoculation volume.

**Table 3 pone.0342275.t003:** Concentration of the different components of the sterile basal fermentation media that will be used for in vitro fermentation experiments in work package 2 of the NORMA study.

Component	Concentration
Peptone water	2 g/L
Yeast extract	2 g/L
NaCl	0.1 g/L
K_2_HPO_4_	0.04 g/L
KH_2_PO_4_	0.04 g/L
MgSO_4_*7H_2_O	0.01 g/L
CaCl_2_*6H_2_O	0.01 g/L
NaHCO_3_	2 g/L
Hemin	0.05 g/L
Vitamin K	10 µ/L
L-cysteine HCl	0.5 g/L
Sodium glycocholate	0.5 g/L
Sodium taurocholate	0.5 g/L
Prebiotic/carbohydrate source	0.5% w/w
ddH_2_O	To 1 L

NORMA, Norwegian microbiota study in anorexia nervosa

#### Fermentation.

Based on the OD_600_ measured during the preparation, the processed anaerobic fecal samples from WP1 will be inoculated to a final OD_600_ of 0.4 into the bioreactors while still in the anaerobic chamber. After 1 hour, the bioreactors will be transferred out of the anaerobic chamber, placed on magnetic stirrers, and connected to the gas inlets and outlets, pH-adjustment tubes, and the water bath. The fermentation will run for 24 hours. Samples taken during the fermentation will be mixed (1:1) with RNAlater (Sigma-Aldrich).

### Hypotheses in WP2

The in vitro fermentation experiments in WP2 will be designed to test the following hypothesis.

WP2, Hypothesis: Carbohydrates with prebiotic potential (e.g., galactoglucomannan) shown to stimulate the growth of bacterial species that have low abundance in AN (e.g., *Roseburia intestinalis, Faecalibacterium prausnitzii, Blautia spp, Bifidobacterium spp, Agathobacter faecis* also known as *Roseburia faecis*) will increase the abundance of these beneficial bacteria in the in vitro culture of AN-derived microbiota.

### The animal experiments (WP3)

#### Mouse groups and timeline.

In WP3, anaerobic fecal samples from patients with AN and HCs, collected in WP1 (see section “Fecal samples”), will be used as donor material for FMT into newly weaned female C57BL/6JRj mice. An initial experiment will include three groups of mice (**Fig 3A**): AN-FMT, HC-FMT, and Sham. Mice in the AN-FMT and HC-FMT groups will receive FMT from AN and HC donors, respectively, via oral gavage. Fecal material from eight AN and eight HC donors will be used for this purpose, and four mice will receive FMT from each donor. All mice in the Sham group will, instead of FMT with fecal material, receive a solution of phosphate-buffered saline with 10% glycerol, serving as a vehicle-only FMT control. Apart from this, the oral gavage protocol will be the same for all mice across the three experimental groups.

The timeline for the initial mouse experiment can be seen in **Fig 3B**. Based on the results from an FMT experiment reported by Le Roy et al. [65], the mice will be approximately three weeks old (i.e., at weaning) at the start of the experiment, targeting the critical period in gut microbiota establishment known as ‘the window of opportunity’. During the first experimental week, mice will receive FMT or Sham treatment on three consecutive days, as done in Le Roy et al. [65]. In the next four weeks, FMT or Sham treatment will be administered once weekly, in accordance with another experiment with FMT from AN donors to mice [38]. After the five-week treatment period, mice will undergo behavioral tests to assess anxiety- and compulsive-like (i.e., repetitive) behaviors using the open field (OF), elevated plus maze (EPM), and marble burying (MB) tests. Body weight and food consumption will be recorded weekly during the experiment, and fecal droppings will be collected before the first FMT/Sham treatment and at the termination day.

At termination, blood will be collected by cardiac puncture to obtain approximately 500–1000 µL of blood. Prior to the procedure, mice will be anesthetized with a single intraperitoneal injection (0.1 mL/10 g body weight) of ZRF cocktail consisting of Zoletil Forte, Rompun, and Fentadon, containing the active ingredients zolazepam (32 mg/kg), tiletamine, xylazine (4.5 mg/kg), and fentanyl (26 µg/kg). Following cardiac blood collection, euthanasia will be ensured by performing cervical dislocation. After euthanasia, intestinal content, brain tissue, and other types of relevant tissues will be collected.

During the initial mouse experiment, housing cages will be enriched with igloos, running wheels, and cardboard tubes. Traffic in the animal facility will be minimized, and personnel will behave calmly and avoid strong odors (e.g., perfume). Animals will be handled as little as possible but will undergo regular handling (e.g., weekly weighing) to acclimate them to routine procedures and minimize stress. Oral gavage for microbial transfer will be performed by experienced personnel to ensure minimal animal suffering. During the first week of gavage feeding (at three weeks of age), mice will receive softened, moistened feed to ensure adequate nutrition immediately after weaning. If weight gain is insufficient, animals will be closely monitored and softened feed will continue beyond the first week of the experiment.

Additional mouse experiments will be performed based on the results of the initial mouse experiment in WP3 and the findings in WP2. Ideally, follow-up experiments will aim to determine whether gut microbiota-modulating interventions, such as prebiotics used in WP2, can normalize AN-associated alterations in the gut microbiota of AN-FMT mice. Such normalization may, in turn, influence other AN-related traits, including behavioral and metabolic phenotypes. However, these experiments will only be pursued if the FMT in the initial experiment successfully induces both AN-associated microbial profiles and relevant phenotypic traits in the recipient mice.

